# The QUILT study: quilting sutures in patients undergoing breast cancer surgery: a stepped wedge cluster randomized trial study

**DOI:** 10.1186/s12885-023-11154-0

**Published:** 2023-07-17

**Keywords:** Mastectomy, Breast cancer surgery, Quilting, Flap fixation, Seroma, Complications, Shoulder function, Pain, Cosmetic outcome, Health care consumption

## Abstract

**Background:**

Seroma is the most common complication following breast cancer surgery, with reported incidence up to 90%. Seroma causes patient discomfort, is associated with surgical site infections (SSI), often requires treatment and increases healthcare consumption. The quilting suture technique, in which the skin flaps are sutured to the pectoralis muscle, leads to a significant reduction of seroma with a decrease in the number of aspirations and surgical site infections. However, implementation is lagging due to unknown side effects, increase in operation time and cost effectiveness. Main objective of this study is to assess the impact of large scale implementation of the quilting suture technique in patients undergoing mastectomy and/or axillary lymph node dissection (ALND).

**Methods:**

The QUILT study is a stepped wedge design study performed among nine teaching hospitals in the Netherlands. The study consists of nine steps, with each step one hospital will implement the quilting suture technique. Allocation of the order of implementation will be randomization-based. Primary outcome is ‘textbook outcome’, i.e.no wound complications, no re-admission, re-operation or unscheduled visit to the outpatient clinic and no increased use of postoperative analgesics. A total of 113 patients is required based on a sample size calculation. Secondary outcomes are shoulder function, cosmetic outcome, satisfaction with thoracic wall and health care consumption. Follow-up lasts for 6 months.

**Discussion:**

This will be one of the first multicentre prospective studies in which quilting without postoperative wound drain is compared with conventional wound closure. We hypothesize that quilting is a simple technique to increase textbook outcome, enhance patient comfort and reduce health care consumption.

## Introduction

### Background and rationale {6a}

The most frequently reported complication after mastectomy and/or axillary lymph node dissection (ALND) is seroma formation. Seroma is a collection of any fluid underneath the skin flaps or in the axillary space after surgery. Seroma incidence following mastectomy is reported to be up to 90% [1–3]. Seroma causes patient discomfort (pain, impaired shoulder mobility, swelling, fear of recurrence), often urging for needle aspirations. This can result in a site of entry for bacteria causing surgical site infections, wound complications and eventually potential delay to adjuvant therapy. It also leads to an increased healthcare consumption due to prolonged hospital stay, more outpatient clinic visits and re-operations [1, 3–7].

Seroma is a much discussed topic in literature and preventive measures are extensively reported. Fibrin glue, bovine thrombin, external compression and shoulder immobilization all seem to be ineffective or at best moderately effective [8–11]. Closure of the dead space after surgery seems to be a key factor in reducing seroma formation [3]. The quilting suture technique, where the skin flaps are fixated to the pectoralis major muscle, decreases the incidence of seroma formation. Quilting is a technique regularly used following flap harvesting in autologous breast reconstruction [12, 13]. Quilting following primary breast cancer surgery is reported increasingly over the past years [6, 14–16]. In studies comparing quilting to the conventional closure, seroma incidence decreased from 81 to 23% [6] and 23 to 8% [17] due to quilting. Also the number of aspirations, volume of aspirations and incidence of surgical site infections, wound edge necrosis, hematoma and re-operations decreased [5–7, 18, 19].

In the vast majority of hospitals mastectomy incision is closed at subcutaneous and skin level over a vacuum drain. Recent evidence, however, suggests that a postoperative drain has no value in reducing seroma formation in combination with the quilting suture technique following mastectomy [7, 20–22].

In addition to diminishing patient discomfort, quilting could decrease healthcare consumption. The omission of drains and the limited complication risk should facilitate the evolution of breast cancer surgery to day care treatment. Seroma related visits to the outpatient clinic, re-admissions and complication related to surgery are likewise expected to decrease.

Despite the first report of success from quilting sutures in 1993, this technique is still not embedded in global daily practice [23]. Surgeons are reluctant to implement the quilting technique because of hypothetical disadvantages of quilting. In the absence of well-founded studies, critics are raised such as increased postoperative pain and decreased shoulder function caused by tight sutures, concerns exist about cosmetic outcome and possible skin dimpling and longer operating time could give raise to increased healthcare costs [16, 24].

To date, no multicenter prospective studies have been published in which quilting without postoperative wound drain is compared with conventional wound closure with postoperative wound drain, reporting on seroma and other potential (dis)advantages.

The objective of this study is therefore, to assess the impact of quilting in patients undergoing mastectomy and/or ALND in nine teaching hospitals. Postoperative complications, shoulder function, cosmetic outcome, satisfaction with thoracic wall, postoperative pain and healthcare consumption of patients treated with the quilting suture technique without drain will be compared with conventional wound closure. All these will be summarized in the primary outcome as textbook outcome. Textbook outcome is achieved if a patient suffers no wound complications, requires no re-admissions or re-operation in relation to primary surgery nor any unscheduled visit to the outpatient clinic and the postoperative use of analgesics after six months is not increased compared to pre-operative.

Textbook outcome is defined as the percentage of patients for whom all desired short-term outcomes of care are realized [25]. This outcome provides a meaningful summary measure of health care quality for patients, providers and insurance companies. It is a useful outcome to make a comparison between different hospitals. Usually significant variability between hospitals can be expected, all scoring well on different single factors, but poorly in other factors. Besides, a compound indicator reflecting the ideal surgical outcome is more meaningful than one single outcome item and it is a useful tool for managing patient expectations [26].

### Objectives {7}

The objective is to report whether implementation of quilting in breast cancer surgery improves textbook outcome. Data is collected on the incidence of seroma and other postoperative complications, postoperative pain, shoulder function and health care consumption.

We hypothesize that implementation of quilting in breast cancer patients undergoing mastectomy and/or an axillary lymph node dissection increases textbook outcome. We expect incidences of seroma and other postoperative wound complications to decrease, with the same cosmetic outcome and without an increase in postoperative pain or impairing shoulder function. Moreover we hypothesize health care costs to reduce as a result of quilting.

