### Outcomes {12}

#### Primary study parameter/endpoint

‘Textbook outcome’ (TO), a combination of outcome parameters reflecting an ideal surgical outcome. Measured 6 months post-operative, the patients postoperative course must comply with the following to meet the definition of TO:no wound complicationsno re-admissions in relation to primary surgeryno re-operation in relation to primary surgery, re-excisions in case of involved margins allowedno unscheduled visit to the outpatient clinic (depending on the centre one or two postoperative visits are usually scheduled)postoperative use of analgesics (6 months) is not increased compared to pre-operative

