#### Secondary study parameters/endpoints

Wound complications are defined by the Clavien Dindo classification of Surgical Complications [27] and scored when necessitating (bed side) treatment or follow-up with additional visits to the outpatient clinic, also if beyond 30-days postoperative.All palpation-detected seromas (non-aspirated), proportion (%)Clinical significant seroma (aspirated seroma), proportion (%)Surgical site infections (SSI), proportion (%)Wound hematoma or bleeding, skin flap necrosis, wound dehiscence, visualized by inspection, proportion (%)

Health care consumption:Duration of surgery: time from incision till wound closed (minutes), meanDuration of hospital stay (treatment in day care or amount of nights, day care classified 0), meanNumbers of unscheduled visits to the outpatients clinic (one postoperative visit is scheduled), medianReadmission to the hospital related to primary surgery, medianReoperation, related to primary surgery other than re-excision, median

Baseline characteristics based on assumed risk factors for formation of seroma [3, 4, 28–31]:Biological gender, proportion (%)Age (years at day of surgery), meanBMI (kg/m^2^), meanWeight of the removed breast (gram), meanPolypharmacy (use of five or more medications daily [32], proportion (%)TNM classification (type 1 to 4, no malignancy, in situ, ypT0N0, angiosarcoma), nominal, proportion per stage (%)Type of surgery (uni- or bilateral mastectomy, ALND or a combination), nominal, proportion per type (%)Prior irradiation of the breast in recurrent breast cancer, proportion (%)Neoadjuvant chemotherapy, proportion (%)

Other:Shoulder function questionnaire (DASH questionnaire = Disability of the Arm, Shoulder and Hand [33], median scorePost-operative pain (visual analogue scale day 1–14 postoperative and use of analgesics), median scoreCosmetic outcome (an independent panel of four surgeons will blindly assess cosmetics by classifying standardised digital photographs one a 4-point Likert scale with the following categories: poor, fair, good and excellent. Photos are taken in two positions: the first in neutral position with both arms hanging next to the body and the second with both arms raised in 180gr (or as far as possible) elevation).Satisfaction with thoracic wall (BreastQ questionnaire for mastectomy [34]), median score

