### Statistical methods

#### Statistical methods for primary and secondary outcomes {20a}

Primary outcome is a binary outcome presented as number of cases and percentage. Nominal data will also be presented as percentage. Continuous data will be presented as mean ± standard deviation or median ± interquartile range, based upon whether the assumption of normality holds (visual interpretation). Analysis of continuous data will be performed by applying the Students T-test for unpaired data in case of continuous variables with a normal distribution. Otherwise the distribution will be compared using the Mann–Whitney U-test. Chi2 test will be used for comparisons of categorical variables between the two groups. The Fisher’s exact test will be performed where applicable. Since data is clustered analysis will be performed using a generalized logistic mixed-effects model with cluster as random intercept. A P-value < 0.05 is considered statistically significant.

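### The expectations of unchanged cosmesis, pain and shoulder function are paired with difference tests that cannot support them, and these domains are wrongly said to be summarised in textbook outcome

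*Protocol article*

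**What the plan says.** **Expectation.** Objectives {7} hypothesises a gain in textbook outcome and expects fewer seromas and wound complications "with the same cosmetic outcome and without an increase in postoperative pain or impairing shoulder function". Background and rationale {6a} gives pain, shoulder function and cosmetic concerns among the reasons why surgeons hesitate to adopt quilting.

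**What textbook outcome is said to contain.** The same background section sets out what will be compared with conventional closure: "Postoperative complications, shoulder function, cosmetic outcome, satisfaction with thoracic wall, postoperative pain and healthcare consumption of patients treated with the quilting suture technique" without a drain. It continues: "All these will be summarized in the primary outcome as textbook outcome". The Discussion similarly presents the primary outcome as reflecting every relevant parameter.

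**What it does contain.** Outcomes {12} lists five conditions: no wound complication, no related re-admission, no related re-operation, no unscheduled outpatient visit, and "postoperative use of analgesics (6 months) is not increased compared to pre-operative".

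**Where the other domains sit.** Under the secondary endpoints, in the group headed Other, are "Shoulder function questionnaire (DASH questionnaire = Disability of the Arm, Shoulder and Hand"), pain ("visual analogue scale day 1–14 postoperative and use of analgesics"), cosmesis ("an independent panel of four surgeons will blindly assess cosmetics" on a 4-point scale) and BreastQ satisfaction.

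**Tests.** Statistical methods {20a} names the t-test, Mann–Whitney, chi-square and Fisher tests, and a logistic mixed model with a random intercept for cluster. Its criterion is "A P-value < 0.05 is considered statistically significant". No margin is given.

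**Size.** Sample size {14} is based on textbook outcome only (30% against 60%). The Discussion nevertheless says shoulder function and cosmetic satisfaction will be reported in a population that is large enough.

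**The concern.** Two statements in the article do not fit together. It expects no deterioration in three domains, and the analysis it fixes for them can show deterioration but cannot show its absence. It also tells the reader that the primary outcome summarises those domains, when most of them are outside it.

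The conclusion most likely to change practice is at stake. If textbook outcome improves and the DASH, VAS and cosmesis comparisons are non-significant, a reader of the background section could believe the surgeons' objections have been answered. The improvement would carry no information on DASH, early pain or cosmesis as measured, and the non-significant tests could be compatible with a relevant worsening.

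**Working it through.** **1. Components against domains.**

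| Domain said to be summarised | In textbook outcome? |
|---|---|
| Postoperative complications | Yes, as wound complications |
| Healthcare consumption | In part: re-admission, re-operation, unscheduled visits |
| Postoperative pain | In part: analgesic use at 6 months; VAS on days 1–14 is not included |
| Shoulder function (DASH) | No |
| Cosmetic outcome (panel) | No |
| Satisfaction with thoracic wall (BreastQ) | No |

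The sentence after the claim in the background section already gives the five-component definition, so the contradiction lies within one paragraph.

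**2. The plan's own sample size.** The printed formula is 2 × (1.96 + 0.8416)² × 0.45 × 0.55 / 0.30² = 43.17, rounded up to 44. With its leading factor 2, it gives patients per arm. The final step, 94 × 1.2 = 112.8, rounds up to 113 as stated. The step from 44 to 94 could not be reproduced from the stated inputs, but nothing below depends on it. The ratio 94/44 should not be used to inflate variances, because it divides a total by a per-arm number. No input concerns pain, shoulder function or cosmesis.

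**3. Precision for a continuous secondary outcome.** The article gives no SDs, so results are in SD units.

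*Best case: 47 against 47, no clustering or time effect.*
- SE = √(2/47) = 0.206 SD
- 95% CI half-width = 1.96 × 0.206 = 0.40 SD
- Power for a true harm of 0.4 SD = Φ(0.4/0.206 − 1.96) = 0.49, so non-significant in 51% of trials

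*Stepped-wedge model (Hussey–Hughes).* Assumptions: 9 clusters, 10 periods (one before the first switch, then nine steps), equal cell sizes, the article's ICC of 0.028 applied to these outcomes, and no transition data dropped.
- SE = 0.279 SD
- 95% CI half-width = 1.96 × 0.279 = 0.55 SD
- Power for 0.4 SD = Φ(0.4/0.279 − 1.96) = 0.30, so non-significant in 70% of trials

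| True harm | Non-significant, no clustering (94) | Non-significant, stepped wedge (94) |
|---|---|---|
| 0.3 SD | 69% | 81% |
| 0.4 SD | 51% | 70% |
| 0.5 SD | 32% | 57% |

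With all 113 patients evaluable, the stepped-wedge half-width is 0.50 SD and a 0.4 SD harm is non-significant in 66% of trials.

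**4. What a margin would demand.** With one-sided 2.5%, 80% power and no true difference, the number per arm is 2 × (1.96 + 0.8416)² / margin² under individual randomisation. Totals are 786 patients for a margin of 0.2 SD, 350 for 0.3, 198 for 0.4 and 126 for 0.5. With 94 patients, the smallest margin reaching 80% power is (1.96 + 0.8416) × SE: 0.58 SD without clustering and 0.78 SD under the stepped-wedge model.

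**The case against.** The strongest reply is that the article sets no formal no-harm objective. Its one stated objective is whether textbook outcome improves, and the clause on cosmesis, pain and shoulder function is an expectation about secondary endpoints. That stands, and it rules out treating this as a failed non-inferiority design.

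A reader might infer that the plan will take P>0.05 as proof of no harm. No section states such a rule. The nearest text is the Discussion's account of the earlier two-centre study, which reports no significant difference in shoulder function, pain and analgesic use. That accurately describes a test result, although its use in answering surgeons' concerns makes the misreading foreseeable.

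A reader might also infer that textbook outcome says nothing about pain. That goes too far. Increased analgesic use at 6 months fails it, and unscheduled visits count without restriction by cause, so a visit for pain or shoulder trouble would fail it too.

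The background sentence can be defended as loose introductory wording, since the correct definition follows at once and anyone coding the endpoint would use that. This limits the harm but does not make the sentence true.

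Finally, margins for secondary endpoints are often left to an analysis plan, and the article does not exclude confidence intervals. An absent margin is therefore not the fault in itself. What remains is the mismatch between the printed expectation and the printed tests, together with two statements, on content and on size, that an analysis plan would not correct.

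**Conclusion.** The point holds in limited form. The planned difference tests at P<0.05 cannot support the expectation of unchanged cosmesis, pain and shoulder function. The background section wrongly says these domains are all summarised in textbook outcome. The claim that the population is large enough for shoulder function and cosmesis has no calculation behind it.

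With 94 evaluable patients, a true harm of 0.4 SD would be missed in about 51% (no clustering) to 70% (stepped-wedge model) of trials. These figures treat the outcome as continuous, so they are approximate for medians and for a 4-point rating. They also rest on an ICC that was estimated from the pilot for the sample size, and dropping data from the expected eight-week transition would reduce precision further. The choice of 0.4 SD is illustrative; the article gives neither an SD nor a relevant difference.

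A demand for formal non-inferiority testing of every such endpoint would be stronger than the documents support, and at this size would mostly fail for lack of precision. The primary analysis of textbook outcome is unaffected. What changes is what may be concluded about harm.

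**What to change.** 1. In Background and rationale {6a}, replace the summarising sentence with the five actual components and say that shoulder function, early pain, satisfaction and cosmesis are assessed separately. Align the matching remark in the Discussion.
2. Drop or qualify the statement that the population is large enough for shoulder function and cosmesis; say that the size was set for textbook outcome only.
3. Report DASH, VAS and cosmesis as quilting effects with 95% CIs, from models suited to each scale that allow for cluster and period. State that P>0.05 will not be read as absence of harm.
4. Claim not impaired for an outcome only if its CI excludes a margin fixed before analysis. Otherwise label the comparison descriptive or inconclusive. Declaring all of them descriptive from the start is a reasonable choice here.

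This costs wording and, where a claim is wanted, a pre-stated margin. It needs no new patients or data. The downside is that most no-harm comparisons will probably be inconclusive at this size.

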### Study design {8}

The QUILT study is a stepped wedge cluster randomized study.

## Methods: Participants, interventions and outcomes

### Study setting {9}

The organizing hospital, Canisius Wilhelmina Hospital, is excluded from participation because the quilting suture technique already is standard care for multiple years. The participating nine hospitals provide standard care by conventional wound closure with postoperative drainage. These nine hospitals will be randomized for implementation of the quilting suture technique as a cluster. With each step every two weeks, one cluster is randomised to implement the quilting suture technique, there will be nine steps. Transition period or learning curve is expected to be 8 weeks. Follow up continues for six months postoperatively (Fig. 1). At T1 all hospitals start including patients.

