### Sample size {14}

To calculate the sample size of a randomized controlled trial TO is assumed to be 30% without quilting, as based upon a pilot study [7]. A doubling of TO is considered clinically significant, resulting in a TO of 60% with quilting. In this study 2 treatment arms will be used, with a significance level of 0.05 and power of 80%. For a parallel randomized trial in which *patients* are randomized, a minimum of 44 patients need to be included:$$2* {\left({\mathrm{Z}}_{\frac{0.05}{2}}+{\mathrm{Z}}_{0.80}\right)}^{2}*\frac{1}{{0.30}^{2}}* 0.45\left(1-0.45\right)=44$$

However, since in the present study *clusters* and not patients are randomized, we need to correct for the fact that outcomes within clusters are very likely more similar than those between clusters. The degree of similarity is estimated using the intra-cluster correlation coefficient (ICC) [35]. This was estimated to be on average 0.028, based upon the pilot study of the 2 hospitals with the variables age, body weight, ASA classification, type of surgery, neo-adjuvant chemotherapy, radiotherapy, tumour classification and first or second episode of breast cancer.

Consequently, the formula as proposed by Hemming et al. was used to correct for this similarity with a total of nine clusters and nine steps [36]. This led to a minimum of 94 patients in total or 11 per centre. A margin safety of 20% was introduced to correct for loss-to-follow-up, which led to a total of 113 patients or 13 per centre. Based on an average of 50 mastectomies each year per centre, the duration of the total inclusion should take 3 months. To correct for the probability of non-adherence to the quilting technique since it is new implemented for all surgeons (safety margin of 20%) each step will take 2 weeks. Suspected transition period and learning curve was suspected to be eight weeks.

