## Discussion

This is the first multicentre prospective study in which quilting without postoperative wound drain will be compared with conventional wound closure with postoperative wound drain following mastectomy and/or axillary lymph node dissection (ALND) with textbook outcome as primary outcome.

To investigate the effect of quilting on quality of health care, a primary outcome parameter is proposed that reflects all relevant parameters and is also suitable for a sample size calculation based on available data from previous studies.

Although often used in previous studies as a primary end-point, seroma can be difficult to define and interobserver variability is likely to occur. Ultrasound could be used to diagnose seroma, however, potential over diagnosis of clinically insignificant small fluid collections would obscure the results. In previous publications the term “clinically relevant seroma” was used to identify those collections necessitating outpatient drainage, often by repeated needle aspiration. This concept is however prone to interobserver subjectivity and physicians’ preference. For these reasons a combined endpoint was defined as an uneventful postoperative course, a so-called textbook outcome following mastectomy and or axillary dissection. Textbook outcome is a multidimensional measure, reflecting an uneventful course following mastectomy and/or ALND. The definition of textbook outcome was established in consultation with surgeons from different hospitals. In this study textbook outcome implies a postoperative course proceeded without wound complications, unscheduled visits to the outpatient clinic, re-admissions, re-operation nor increased use of analgesics compared to pre-operative, measured 6 months post-operative.

The sample size in the protocol is based on data from a previous performed study in two participating hospitals: CWZ and RH [7]. The incidence of textbook outcome was determined from data in both hospitals, where one hospital (CWZ) applied quilting sutures without postoperative drainage as standard practice and the other hospital (RH) used conventional wound closure with postoperative drainage as standard practice.

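### An 8-week learning period (four steps) is expected, but the sample size of 113 assumes the full effect from each switch, and neither the size nor the stated model allows for it

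*Protocol article*

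**What the plan says.** Study setting {9} describes nine hospitals, with one switching to quilting every two weeks over nine steps and all hospitals including patients from T1. It then states: "Transition period or learning curve is expected to be 8 weeks".

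Sample size {14} fixes the two rates: "TO is assumed to be 30% without quilting", and a doubling is the clinically relevant gain, "resulting in a TO of 60% with quilting". The clustering formula "was used to correct for this similarity with a total of nine clusters and nine steps" and gives 94 patients, then 113 after a 20% margin for loss to follow-up. A second 20% margin, for non-adherence, is tied to step length. The section closes with "Suspected transition period and learning curve was suspected to be eight weeks", and no term, exclusion or inflation follows from it.

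Statistical methods {20a} gives a logistic mixed model with a random intercept for cluster. It mentions no transition and no time since switch. Section {20c}, on non-adherence and missing data, does not mention the learning period. Section {11b} excludes patients whose surgeon refrains from quilting, including for lack of expertise. Patients who are quilted by a surgeon still learning stay in.

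**The concern.** A learning period of four steps is long relative to a nine-step rollout. Three treatments of the early patients are possible: count them as fully quilted, leave them out, or model them separately. Each gives a different estimand and a different power, and the protocol names none of them. In an unblinded trial the choice could then be made with the data in view.

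A later analysis plan could add a model term or a handling rule. It cannot restore power to a sample size already fixed on an immediate, full 30-point difference.

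**Working it through.** **The plan's own figures.** 2 × (1.960 + 0.842)² × 0.45 × 0.55 / 0.30² = 43.2, rounded up to 44, as stated. (This formula gives a number per arm, whereas the text presents 44 as the total; that is a separate point.) 94 × 1.2 = 112.8, so 113 also reproduces. The 94 does not reproduce from the closed-form stepped-wedge design effect with nine clusters, nine steps, one baseline period and ICC 0.028: solved self-consistently, that gives about 79 starting from 44, or about 172 starting from 88. A linear mixed model with hospital intercepts only and an immediate full effect needs 90 for 80% power, which is close to 94. No variant tried contains a transition allowance.

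**Share of quilting data in the first 8 weeks.** Take one control period, then hospital k (1 to 9) quilting from period k, with inclusion ending at period 9.
- Quilting hospital-periods: 9 + 8 + … + 1 = 45.
- Later than the first four periods after the switch: 5 + 4 + 3 + 2 + 1 = 15, all in hospitals 1 to 5.
- Inside the first 8 weeks: 45 − 15 = 30, or 67%. Hospitals 6 to 9 have no later data.
- Post-learning quilted patients: 113 × 15/90 ≈ 19.

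If inclusion runs on for 2, 4, 6, 8 or 16 further weeks, the share is 61%, 56%, 50%, 44% or 31%. If inclusion really stopped at the 3 months given in Sample size {14} (6 to 7 periods), it would be 86 to 93%.

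**Power.** This is generalised least squares on the proportion scale with even accrual and no losses. The total variance is 0.45 × 0.55 = 0.2475 and the between-hospital part is 0.028 × 0.2475 = 0.0069. There are 113/90 = 1.26 patients per hospital-period. Power = Φ(effect/SE − 1.96). Inclusion ends with the last step.

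| Scenario | As written (no time term) | With period effects |
|---|---|---|
| Immediate full effect | 30 points, SE 0.096: 88% | 30 points, SE 0.128: 65% |
| First 8 weeks dropped | 30 points, SE 0.137: 59% | 30 points, SE 0.229: 26% (32% with linear time) |
| Kept, half effect for 8 weeks (assumed) | 19.6 points, SE 0.096: 54% | 16.5 points, SE 0.128: 25% |

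With half effect the plain average over quilting patients is (30 × 15 + 15 × 30)/45 = 20 points. The model as written returns about that average; with period effects the estimate leans further towards early exposure.

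**Range for the undocumented learning-phase effect, as written.** Full effect gives 30 points and 88%. Half gives about 20 points and 54%. Nil gives about 9 points and 16%.

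**Eight more weeks of inclusion at the same accrual rate** (so more than 113 patients). Dropping the transition gives 88% without a time term and 26 to 34% with one. Keeping the patients at half effect gives 79% without a time term.

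**The case against.** Several points on the other side are sound.

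- **The aim is implementation.** The abstract and Objectives {7} ask what implementing quilting does, and that effect can properly include learning. A step shorter than the learning period is not in itself an error.
- **The 30 points are a relevance threshold.** Sample size {14} justifies 60% as a clinically significant doubling and never labels it post-learning. The Discussion says the pilot drew on two hospitals, "where one hospital (CWZ) applied quilting sutures without postoperative drainage as standard practice". This suggests established practice, but it does not make 30 points the post-learning effect by definition.
- **The learning-phase effect is unknown.** The technique is described as straightforward, with video and on-site teaching. Learning might affect operating time more than textbook outcome.
- **The worst power figures need a time term that the stated model lacks.** Part of that loss comes from the term itself: 88% falls to 65% with no learning period at all.
- **Accrual may be higher.** At 50 mastectomies per centre per year (50/26 = 1.92 per two weeks), 90 hospital-periods hold about 173 patients. Dropping the transition then gives 76% as written, or 36 to 43% with time.
- **Fig. 1 is not shown.** It may mark transition periods or a longer tail.

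These points limit the size of the problem. They do not supply an allowance: a figure would not change the written calculation, and neither 20% margin covers a smaller effect while surgeons learn.

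**Conclusion.** The gap is real and worth correcting. The protocol states a four-step transition, sizes the trial as if there were none, and does not say how the affected patients are analysed. With inclusion ending at the last step and 113 patients, power under the model as written falls from 88% to 59% if they are dropped, and to 54% if they are kept at half effect. If they are kept and already have the full effect, nothing is lost.

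A reader might infer more than the documents support:
- That most quilting data are necessarily learning-phase data. This depends on how long inclusion continues; at 6 or more extra weeks the share is 50% or less.
- That the trial cannot estimate 30 points. This depends on a learning-phase rate that the documents do not give.
- That 80% power is unattainable either way. With 8 more weeks of inclusion and no time term, dropping the transition still leaves 88%.

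All power figures are linear-scale approximations with even accrual, ICC 0.028 and no loss to follow-up.

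**What to change.** 1. State that every patient quilted after the hospital's switch date counts as quilting in the primary analysis, so that the primary effect is that of implementation, learning included.
2. Add a prespecified secondary analysis with a time-since-switch term (first 8 weeks versus later).
3. Restate the power at 113 for the implementation effect over a stated range of learning-phase effects, and separately for the later-phase effect. State how long inclusion continues after the last step.

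The 30 points should not simply be relabelled as post-learning while implementation stays primary, because the primary effect would then have no sample size behind it.

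The cost is some wording, one extra model term and a less favourable stated power. The later-phase estimate will be imprecise: on the text schedule it rests on about 19 patients in five hospitals.
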